## Abstract

**Background:**

Breast cancer patients often experience significant concerns regarding surgery, which predisposes them to negative emotions such as anxiety, adversely affecting both surgical outcomes and postoperative recovery. However, research on interventions for perioperative anxiety remains limited. This study focuses on patients undergoing radical mastectomy to investigate the effects of transcutaneous auricular vagus nerve stimulation (taVNS) on perioperative anxiety, aiming to provide novel clinical strategies for its prevention and management.

**Methods:**

This prospective, double-blind, randomized controlled trial will enroll 202 eligible patients with radical mastectomy. Patients are randomly assigned to either the treatment group (taVNS group) or the control group (sham stimulation group). In treatment group, taVNS is administered 30 min before anesthesia induction and at the same time point daily for postoperative days 1–3, using specific stimulation parameters. The control group was given a sham stimulus. Primary outcome is the perioperative anxiety remission rate, which assessed by comparing post-intervention (after the final session) and pre-intervention (before the first session) scores in patients subjected to either full-course taVNS or sham stimulation. Secondary outcomes are Hamilton Anxiety Rating Scale (HAMA), Pittsburgh Sleep Quality Index (PSQI), 3-Minute Diagnostic Interview for Confusion Assessment Method-Defined Delirium (CAM-3D), Numerical Rating Scale (NRS), Fatigue, Resistance, Ambulation, Illnesses, and Loss of Weight (FRAIL) and heart rate variability (HRV).

**Discussion:**

The strength of this study lies in the adoption of taVNS as an intervention for perioperative anxiety and the establishment of a comprehensive efficacy evaluation system. taVNS may alleviate anxiety by modulating autonomic nervous function and restoring the balance between sympathetic and parasympathetic activity. This study aims to provide an innovative approach for mitigating perioperative anxiety, with the potential to improve patient outcomes and enhance quality of life.

**Clinical trial registration:**

https://www.chictr.org.cn/indexEN.html, Identifier ChiCTR2500106867.

## Introduction

1

Breast cancer remains one of the most significant global health challenges. According to the latest report from the World Health Organization (WHO) International Agency for Research on Cancer (IARC), breast cancer ranks as the second most prevalent malignant tumor worldwide (1). China accounts for the highest number of breast cancer cases, representing approximately 18.4% of the global burden (2), which imposes substantial adverse impacts on public health and socioeconomic development in the country. Currently, the primary treatment strategy for breast cancer remains surgical intervention (3, 4). As a major negative life event, radical mastectomy can induce psychological distress such as anxiety and depression in patients. Previous studies have demonstrated that approximately 41.9% of breast cancer patients experience perioperative anxiety (5). Research indicates that compared to patients with malignancy alone, those with perioperative emotional disorders exhibit a 19% increase in mortality (6), along with elevated treatment-related adverse effects and diminished therapeutic efficacy. Consequently, early intervention for perioperative anxiety is of critical importance.

Currently, both pharmacological and non-pharmacological approaches are commonly employed in clinical practice to alleviate perioperative anxiety. However, anxiolytic medications may induce respiratory depression and prolong recovery time, thus their routine preoperative administration is not recommended (7). Non-pharmacological interventions, such as psychotherapy and self-regulation techniques, are being increasingly implemented in clinical settings. Additionally, non-invasive neuromodulation technologies have demonstrated considerable potential in mitigating perioperative anxiety in patients (8).

In 2000, Canadian scholar Ventureyra developed transcutaneous auricular vagus nerve stimulation (taVNS) based on auricular acupuncture theory, anatomical principles, and traditional vagus nerve stimulation techniques. Compared with conventional invasive approaches, taVNS demonstrates superior safety, lower cost, and greater operational simplicity, establishing itself as a prominent adjunctive therapy. The core mechanism of taVNS involves modulation of autonomic nervous system function and homeostasis, pioneering a novel therapeutic paradigm targeting the peripheral nerve-brain network for systemic regulation. Clinical breakthroughs have been achieved in treating insomnia, depression, and epilepsy (9). Heart rate variability (HRV), defined as the variation in time intervals between consecutive normal heartbeats, serves as a standardized method for assessing autonomic nervous function. This metric offers continuous, objective, sensitive, and noninvasive monitoring advantages (10, 11).

Currently, there is limited research on the application of taVNS in perioperative anxiety management. This study selected patients undergoing radical mastectomy for breast cancer to investigate the efficacy of taVNS in alleviating preoperative anxiety. The mechanistic underpinnings were further explored through HRV monitoring, aiming to provide novel insights for postoperative rehabilitation strategies.

## Methods and analysis

2

### Study design

2.1

This prospective randomized controlled trial will enroll 202 patients scheduled for radical mastectomy at our institution. Using a computer-generated randomization table, eligible participants will be allocated in a 1:1 ratio to either the treatment group (taVNS group) or the control group (sham stimulation group). The trial flow chart is shown in Figure 1. All participant characteristics and clinical outcomes will be documented using case report forms (CRFs). Data collection procedures are outlined in Table 1.

**Figure 1 fig1:**
[figure not shown]
Flow chart of the study. taVNS, transcutaneous auricular vagus nerve stimulation; HAMA, Hamilton Anxiety Rating Scale; PSQI, Pittsburgh Sleep Quality Index; CAM-3D, 3-Minute Diagnostic Interview for Confusion Assessment Method-Defined Delirium; NRS, Numerical Rating Scale; FRAIL, Fatigue, Resistance, Ambulation, Illnesses, and Loss of Weight; HRV, heart rate variability.

**Table 1 tab1:** Schedule of enrolment, interventions, and assessments.

Procedure	Study period						
	T0	T1	T2	T3	T4	T5	T6
Enrolment							
Eligibility screen	✓						
Informed consent	✓						
Allocation	✓						
Randomization	✓						
Interventions							
taVNS							
Sham stimulation							
Assessments							
HAMA	✓	✓	✓	✓	✓	✓	✓
CAM-3D			✓	✓	✓	✓	
NRS			✓	✓	✓	✓	
FRAIL				✓	✓	✓	
PSQI				✓	✓	✓	
HRV	✓	✓	✓	✓	✓	✓	
Adverse events	Throughout the study period until discharge						

taVNS, transcutaneous auricular vagus nerve stimulation; HAMA, Hamilton Anxiety Rating Scale; PSQI, Pittsburgh Sleep Quality Index; CAM-3D, 3-Minute Diagnostic Interview for Confusion Assessment Method-Defined Delirium; NRS, Numerical Rating Scale; FRAIL, Fatigue, Resistance, Ambulation, Illnesses, and Loss of Weight; HRV, heart rate variability. T0, before the initial taVNS or sham stimulation; T1, after the initial taVNS or sham stimulation; T2, 2 h after surgery; T3, 1 day after surgery; T4, 2 day after surgery; T5, 3 day after surgery; T6, 30 day after surgery.

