## Procedure

3

Participants will be screened from the elective surgery roster by the research team. At 30 min prior to anesthesia induction and at the same time point daily for postoperative days 1–3, patients will be subjected to either taVNS (treatment group) or sham stimulation (control group).

*Treatment group*: Electrical stimulation will be applied through electrodes placed on the cymba conchae. Following clip placement, taVNS will be administered for 30 min per session. The device will be activated with the following parameters:

Waveform: Dense-disperse wave.Mode: Constant voltage.Frequency: 20 Hz.Pulse width: 0.2 ms.Intensity: Subthreshold current (maximally tolerated without eliciting sharp pain).

*Control group*: The electrodes will be positioned identically, and the current will be increased over 30 s until the participant reported a tingling sensation. Then reduced to a level just below this perceptual threshold. The device remain off for the subsequent 30 min to simulate the sham condition (12).

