### Primary outcome

4.1

The primary outcome is perioperative anxiety alleviation rate in patients subjected to either full-course taVNS or sham stimulation before the first intervention and after the last intervention. The anxiety alleviation rate will be calculated as follows: (baseline score − post-intervention score)/baseline score × 100%.

Perioperative anxiety will be assessed using the Hamilton Anxiety Rating Scale (HAMA), a 14-item scale with a total score ranging from 0 to 56. The severity of anxiety will be categorized as follows: total score <7: no anxiety; total score 7–13: mild anxiety; total score 14–20: moderate anxiety; total score >20: severe anxiety.

Patient anxiety will be assessed before (T0) and after (T1) the initial taVNS or sham stimulation. Further assessments occurr at 2 h post-surgery (T2), following the intervention on postoperative days 1 to 3 (T3–T5), and at 30 day after surgery (T6).

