### Study safety

5.2

Adverse events related and unrelated to taVNS will be recorded: skin erythema or rash, discomfort at the electrode site, dizziness, nausea, bradycardia, tinnitus, or hearing changes.

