## Discussion

7

To the best of our knowledge, this study represents the first systematic evaluation of the clinical efficacy and safety of taVNS for perioperative anxiety within the framework of a randomized controlled clinical trial (RCT) in China. The findings are expected to facilitate more effective management of perioperative anxiety, thereby improving patient outcomes and guiding clinical decision-making.

The autonomic nervous system (ANS), comprising the sympathetic nervous system and parasympathetic/vagus nerve, serves as a profound homeostatic regulatory system and constitutes a core component of emotional states. It reflects both vulnerability and resilience to psychological and physical health challenges (13, 14). Several disease-specific studies have demonstrated a close association between autonomic activity and emotional states such as depression and anxiety (15). Thayer and Lane (16) proposed that sympathetic activity serves as a determinant of emotional states, with the classic autonomic efferent pattern during emotional responses characterized by increased sympathetic activity coupled with decreased parasympathetic activity. In contrast, Jarrett et al. (17) suggested that negative emotional states (e.g., anxiety and depression) are exclusively associated with reduced parasympathetic tone. Consequently, the precise mechanisms underlying perioperative anxiety remain unclear, though they may involve disruption of ANS homeostasis.

The auricular branch of the vagus nerve represents the sole cutaneous branch of the vagus nerve. According to modern anatomical theory, the auricle is richly innervated, with nerve fibers predominantly concentrated in the cymba conchae, cavum conchae, and triangular fossa. Notably, the auricular concha region contains the only cutaneous vagal afferent fibers in humans. Experimental studies employing horseradish peroxidase (HRP) retrograde tracing of sensory neurons have untangled a potential neural pathway between the vagus nerve in the auricular concha region and the sympathetic ganglia innervating visceral organs. Furthermore, HRP labeling experiments have demonstrated that stimulation of the auricular concha region transmits signals to the nucleus tractus solitarius and medulla oblongata in the brainstem (18).

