## Limitations

8

This study also has limitations. First, due to resource constraints, our assessment of anxiety relief was limited to the first three postoperative days. This timeframe is adequate for evaluating short-term therapeutic effects, but it may not fully capture long-term treatment outcomes. Second, the stringent inclusion criteria may restrict the generalizability of our findings to broader populations. Thirdly, the definition of a “subthreshold current” as the maximum intensity tolerated without eliciting sharp pain introduces substantial inter-patient variability that lacks standardization. This subjectivity represents a well-recognized challenge in non-invasive neuromodulation research. Therefore, real-world studies with extended follow-up and expanded patient populations will be conducted in the future.

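### Adverse-event recording stops at discharge, which has no fixed day, although patients are assessed again at day 30, so events after discharge are not collected

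*Protocol article*

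**What the plan says.** The adverse-event row of Table 1 reads "Throughout the study period until discharge". The columns of that table run to T6, which its footnote defines as "T6, 30 day after surgery". HAMA is the only assessment ticked at T6; the other scales and HRV stop at T5, postoperative day 3. Sections 4.1 and 4.2.1 also place a HAMA assessment at T6.

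Section 5.2 says "Adverse events related and unrelated to taVNS will be recorded" and names skin, electrode-site, vestibular, cardiac and hearing events. It sets no time window of its own, so Table 1 is the only rule on when recording ends. Section 3 gives stimulation before induction and then "at the same time point daily for postoperative days 1–3". Section 7 (Discussion) presents the trial as the "first systematic evaluation of the clinical efficacy and safety of taVNS for perioperative anxiety" in a randomised trial in China.

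**The concern.** Discharge is a weak end point for safety recording for two reasons.

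- It cuts off collection. Whatever begins or continues after the patient goes home is not recorded, and no later analysis plan can recover data that were never collected. Several listed events (rash, tinnitus, hearing change) can outlast a session. A patient who left on day 3 would be observed for only hours after the last session.
- It is a post-randomisation time that varies by patient. The trial measures anxiety, pain, delirium and frailty, any of which could influence when a patient leaves. If stay differed by arm, crude incidences to discharge would be taken over unequal follow-up.

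What is at stake is how far the safety claim in the Discussion can reach. Efficacy is not involved.

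**Working it through.** **Does the plan give a figure to reproduce?** Not on this point: the article states no length of stay and no expected adverse-event rate. The sample size of 91 per group rests on response rates of 50% and 30% and reproduces with unpooled variances: (0.25 + 0.21) × (1.960 + 0.842)² / 0.20² = 90.26, rounded up to 91. Nothing below changes it.

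**Step 1: which days are covered.** Sessions run from before induction to postoperative day 3 (section 3). HRV at T5 is measured on an analyser, in seated patients with nursing help (section 4.2.2). Patients who complete the schedule are therefore very likely still in hospital at T5. The article does not say so outright, so this is an inference.

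**Step 2: which days are not covered.** T5 is day 3 and T6 is day 30, so 30 − 3 = 27 days lie between them. If a patient leaves on day L, recording covers L − 3 of those 27 days, and L of the 30 postoperative days. The discharge days below are assumptions.

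| Assumed discharge day L | Days observed after T5 (L − 3) | Share of 27 days | Share of 30 days (L/30) |
|---|---|---|---|
| 3 | 0 | 0% | 10% |
| 5 | 2 | 7% | 17% |
| 7 | 4 | 15% | 23% |
| 10 | 7 | 26% | 33% |
| 14 | 11 | 41% | 47% |

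With recording through T6, every patient followed to T6 has all 27 days.

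**Step 3: when would the arms be distorted?** Suppose the same constant event rate r per day in both arms and observation for d days, so that observed incidence is 1 − exp(−r·d). Rates and stays are again assumptions.

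- r = 0.01, 5 days in both arms: 4.9% and 4.9%, ratio 1.00.
- r = 0.01, 4 and 5 days: 3.9% and 4.9%, ratio 0.80.
- r = 0.01, 4 and 7 days: 3.9% and 6.8%, ratio 0.58.
- r = 0.03, 4 and 7 days: 11.3% and 18.9%, ratio 0.60.
- r = 0.01, both arms cut at day 3: 1 − exp(−0.03) = 3.0% in each, ratio 1.00.

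The distortion comes entirely from the assumed difference in stay. It vanishes when stays are equal or when a common window is used. A constant rate is also a poor model for acute device effects once stimulation has ended, so these ratios show the mechanism and do not estimate this trial's error.

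**Step 4: is there another rule elsewhere?** No section extends adverse-event recording to T6. Section 8 says "our assessment of anxiety relief was limited to the first three postoperative days". That concerns anxiety, not safety, and itself sits awkwardly with HAMA at T6.

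**The case against.** The best case for the plan is that recording to discharge suits four sessions of a non-invasive device. Most listed events are local or acute and would appear during or soon after stimulation, when patients are probably in hospital. Day-30 reports would mix in surgical complaints and faulty recall, which could dilute a device signal. Safety is not among the listed outcomes, section 6 names no adverse-event test, and tabulation by window can be left to an analysis plan. Most of this stands, and it keeps the point minor. It does not remove it: the end of recording is a stated collection rule, not a detail left for later.

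A reader might infer three stronger things, none of which the document supports.

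- *That the Table 1 row contradicts itself.* The natural reading is that discharge limits the preceding phrase. The wording is loose, but it gives staff one workable rule.
- *That the safety comparison is biased.* This needs stay to differ by arm and events to keep accruing after day 3. The article gives no evidence of either. Section 2.6 blinds patients and healthcare providers other than those delivering the intervention, so discharge should not follow knowledge of allocation. An effect of treatment itself on stay is not excluded, but it is not shown either.
- *That the unobserved share of the 30 days measures missed device harm.* Assuming discharge on day 3 to 7, that share is 90% to 77% (27/30 to 23/30). It rests on assumed discharge days, and its denominator is mostly days without stimulation.

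**Conclusion.** The point holds in a limited form. Safety recording ends at a patient-specific time with no fixed day, although a later assessment is already scheduled. Events after discharge go uncollected, and the period observed after T5 differs between patients. Coverage of T0 to T5 is probably adequate, assuming patients stay through day 3.

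The number of events missed cannot be estimated, because neither length of stay nor late-event rates are given. The loss of post-discharge events occurs even if stays are equal; between-arm distortion is conditional on unequal stays and remains open. The result is a safety statement that can speak only for the hospital stay. The primary outcome, its analysis and the sample size are untouched. This is an inexpensive improvement rather than a flaw that threatens the trial.

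**What to change.** 1. Change the adverse-event row of Table 1 to run from T0 through T6.
2. At the T6 contact, ask every patient about the events listed in section 5.2, in the same words in both arms, and record date of onset and whether the event has resolved.
3. Report adverse events by arm over two windows that do not depend on discharge: T0 to T5, and after T5 to T6. Keeping them apart stops late surgical complaints from diluting events during the stimulation days.
4. Align the follow-up sentence in section 8 with the HAMA assessment at T6, so that it is clear the day-30 contact takes place.

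The cost is a few questions and a small addition to the case report form at a contact already planned. The downside is that day-30 answers depend partly on recall and may reflect surgery rather than the device; with patients and assessors blinded, this should affect both arms alike. The article puts recruitment from August 2025 to August 2026, so an amendment within that period would reach only the remaining patients. For those already past T6, the T0 to T5 window can still be reported, provided that in-hospital events were dated.

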### Sample size

2.2

According to the Chinese Guidelines for the Prevention and Treatment of Anxiety Disorders, which define “a response rate ≥50% as effective and <30% as ineffective.” This study hypothesized response rates of 50% in the treatment group and 30% in the control group. With a statistical power of 0.80 and a significance level of 0.05, sample size calculation using PASS 15.0 software indicated that 91 patients will be required per group. Accounting for a 10% dropout rate, we plan to enroll 101 participants per group, totaling 202 subjects.

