## Statistical analysis

6

Statistical analysis will be performed using SPSS 23.0 (IBM Corp, Armonk, NY, United States). The normality of continuous variables was assessed using the Kolmogorov–Smirnov (K–S) test. Normally distributed data were expressed as mean ± standard deviation (SD). One-way analysis of variance (ANOVA) was employed for multiple group comparisons, while the independent t-test was used for pairwise comparisons between groups. Paired *t*-test was applied for within-group comparisons. Non-normally distributed data were presented as median (interquartile range) and analyzed using nonparametric rank-sum tests. Categorical variables were compared using the chi-square test. A two-tailed *p*-value <0.05 was considered statistically significant.

The primary outcome measure will be analyzed using the intention-to-treat (ITT) principle. Missing data for the primary outcome were handled using multiple imputation by chained equations under the missing-at-random assumption. The interpolation model includes all the analytical variables as well as any auxiliary variables that may be related to the detachment. We generated imputed datasets using the mice package in R. The results from the imputed datasets were combined using Rubin’s rules.

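### The sample size is calculated for response rates of 50% versus 30%, but the primary outcome is defined as a continuous percentage reduction in HAMA, so the stated 80% power does not belong to it

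*Protocol article*

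**What the plan says.** Section 2.2 (Sample size) cites a Chinese guideline that grades "a response rate ≥50% as effective and <30% as ineffective". The next sentence takes the same two figures as the expected result in each arm: "This study hypothesized response rates of 50% in the treatment group and 30% in the control group". Power is set at 0.80 and alpha at 0.05, and the PASS calculation "indicated that 91 patients will be required per group". The section closes: "Accounting for a 10% dropout rate, we plan to enroll 101 participants per group, totaling 202 subjects".

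Section 4.1 (Primary outcome) describes something else. "The anxiety alleviation rate will be calculated as follows": baseline score minus post-intervention score, divided by baseline score, times 100%. The score is the HAMA total, range 0 to 56. The result is one percentage per patient, and 4.1 names no value of it that counts as a response.

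The abstract uses another word: "Primary outcome is the perioperative anxiety remission rate". It explains this only as a comparison of scores before the first session and after the last. The Discussion speaks of a relief rate.

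The Statistical analysis section (6) gives t-tests and rank-sum tests for continuous data and a chi-square test for categorical data. It states "A two-tailed *p*-value <0.05 was considered statistically significant".

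**The concern.** A sample size supports a trial's main conclusion only if it was calculated for the variable that the conclusion rests on. Section 2.2 needs a yes/no status for each patient, so that 50% and 30% can be proportions of patients. Section 4.1 supplies a number on a continuous scale. Power for that number depends on a difference in means and a standard deviation, and the article gives neither.

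A second weakness lies inside 2.2. The guideline figures are bands for grading a result. Where a band begins says nothing about how many patients in either arm will reach it, yet the band limits become the assumed arm proportions with no other support.

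At stake is whether readers can rely on the 80% figure for the trial's single primary comparison. The two sections also lead to different effect measures: a difference in proportions, or a difference in mean or median percentage reduction. A statistical analysis plan that followed one section would depart from the other.

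**Working it through.** **Inputs.** From 2.2: 50% and 30%, power 0.80, alpha 0.05, 91 per group, 10% dropout, 101 per group. From section 6: two-sided testing. From 2.1: 1:1 allocation. Not given anywhere: an SD or expected mean for the percentage reduction.

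**1. Reproduce the plan's figure.** Two proportions, unpooled variance:

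n = (1.960 + 0.842)² × [0.50 × 0.50 + 0.30 × 0.70] / (0.50 − 0.30)²

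= 7.849 × 0.46 / 0.04 = 90.26, rounded up to **91** (7.849 uses unrounded quantiles).

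This matches exactly. The pooled version gives 93. Power at 91 per group is 80.3% unpooled and 79.1% pooled. For dropout, 91 / 0.9 = 101.1, and the plan uses 101; the rounding is immaterial.

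**2. Is the match unique?** No. Proportions of 0.70 and 0.50 have the same variance sum (0.21 + 0.25 = 0.46) and the same difference, so they also give 91. So does a 20-point difference in means with an SD of about 48 (step 3). Section 2.2 does not name its test. A two-proportion calculation is the natural reading of its wording and reproduces the number, but it remains an inference.

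**3. Power for the outcome in 4.1.** For a difference D in mean percentage reduction with common SD, normal approximation:

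power = Φ( D / (SD × √(2/91)) − 1.960 ), with √(2/91) = 0.1483.

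Read 50% and 30% as mean reductions, so D = 20 points. Both this reading and the SDs are assumptions.

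| Assumed SD | 20 / (SD × 0.1483) | Power at 91 per arm | n per arm for 80% power |
|---|---|---|---|
| 40 | 3.37 | 92% | 63 |
| 48 | 2.81 | 80% | 91 |
| 50 | 2.70 | 77% | 99 |
| 60 | 2.25 | 61% | 142 |

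A t-based calculation adds about one patient per arm (64, 100 and 143 for SD 40, 50 and 60).

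**4. What 91 per arm can detect.** (1.960 + 0.842) × 0.1483 = 0.415 SD by the normal approximation and 0.418 by the t-test, so a standardised difference of about 0.42 with 80% power.

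**5. A more favourable reading.** Suppose the percentage reduction is normal with equal SDs, and 50% and 30% are the shares of patients above a common cut-off. The standardised difference is then z(0.50) − z(0.30) = 0.524. Power for the means at 91 per arm is Φ(0.524 / 0.1483 − 1.960), about 94%.

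Steps 3 and 5 show that the power for the defined outcome may lie above or below 80%, depending on inputs that the article does not state.

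**The case against.** The best defence is that 2.2 does contain a candidate cut-off. The guideline wording can be read as a grading of each patient's percentage reduction, with 50% or more counting as effective. The formula in 4.1 would then be the first step towards a responder rate, and the calculation would fit. That reading is plausible, and it shapes one of the two repairs below. But 2.2 uses the figures as arm proportions, 4.1 does not refer back to them, and no section says that the primary comparison is of patients above 50%. The link is missing from the text.

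Several stronger readings are tempting and do not stand:

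- *The trial is underpowered.* The documents do not show this. The 77% and 61% rest on assumed SDs of 50 and 60; smaller SDs, or step 5 above, give more than 80%.
- *Remission in the abstract is a separate endpoint, HAMA below 7.* Section 4.1 labels that band as no anxiety. The abstract ties its term only to the same before-and-after comparison, so loose vocabulary for one measure is the simpler explanation.
- *The endpoint or test could be picked after the data are seen.* Assigning a test is commonly left to an analysis plan, which is not shown. The t-test and rank-sum test also serve the same continuous outcome, so listing both does not create extra endpoints.

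An unseen analysis plan does not remove the core point, because it cannot agree with both 2.2 and 4.1 as they are written.

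**Conclusion.** The point holds as a contradiction between two sections. Section 2.2 sizes the trial on proportions of responders, and its arithmetic is sound for that purpose. Section 4.1 defines a continuous percentage reduction without linking it to any response threshold. The stated 80% power is therefore not shown for the primary outcome as defined.

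The size of the discrepancy cannot be fixed from the document. On the assumption of a 20-point mean difference, power at 91 per arm is about 92%, 77% or 61% for an SD of 40, 50 or 60, and reaches at least 80% for any SD up to about 48. The proper conclusion is that power for this endpoint is unstated, which is different from inadequate. It still needs correcting, because it concerns the single primary comparison. Separately, the 50% and 30% need a basis other than the guideline's grading limits.

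**What to change.** Make a dated amendment before unblinding that names one primary endpoint in 2.2, 4.1 and the abstract, and uses one term in place of response, alleviation, remission and relief. Two routes are open:

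- **(a) Binary.** Define a responder as a patient whose HAMA score falls by at least 50% from T0 to T5 (after the last session), and compare responder proportions between arms. N = 202 stays. State 50% and 30% as assumptions and justify them separately from the guideline cut-offs, for example from earlier trial or pilot data. Continuous HAMA becomes a named secondary outcome.
- **(b) Continuous.** Keep the percentage reduction in 4.1 and delete the 50%/30% power statement. State instead that 91 evaluable patients per arm give 80% power for a standardised difference of about 0.42, and give the expected mean difference and SD behind it. The 0.42 alone is derived from N and justifies nothing.

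**Cost.** A protocol amendment and a matching update of the registry entry, with no new assessments, since HAMA is already scheduled at T0 and T5. Route (a) changes the type of the primary outcome after recruitment began (August 2025, under Trial status), so the amendment should give its date and reason. Route (b) keeps N only if the justified inputs support a standardised difference of about 0.42 or more; a 20-point difference with an SD of 50 or 60 would need about 100 or 143 evaluable patients per arm.
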